### Veteran outcomes and provider experiences

#### Housing stability

We will use VA administrative data to assess housing outcomes for HEVs at our implementation sites. We conceptualize housing stability as our primary effectiveness outcome, strongly associated with substance use frequency and intensity [5–8], which are salient expected outcomes of both EBPs that cannot be reliably abstracted from VA administrative data. We will partner with the Scientific Approaches to Improving Housing and Economic Security Outcomes Advanced by a Learning Health System through Data driven Evaluation and Research (SHELTER) [48], which used natural language processing (NLP) and structured EHR data to build a common longitudinal dataset of HEVs’ housing situations, clinical characteristics, and other social determinants of health. This dataset combines elements across VA and non-VA data pertaining to homelessness and provides longitudinal housing data for all HUD-VASH Veterans available for research studies.

Impacts on housing will be defined as a difference in the mean days homeless over 1 year of follow-up for HEVs enrolled in CARE-VASH sites that received REP vs. REP + CE, versus the expected number of days homeless had they enrolled in a comparison group of all sites not engaged in CARE-VASH. A binary indicator of homelessness will be extracted from SHELTER each day there is EHR documentation of housing status. We will fit a logistic regression model, with an indicator of site assignment (comparison group, REP, REP + CE) as an independent variable, while controlling for HEV characteristics, co-morbidities, temporal trends in the risk of homelessness, and variation across sites. To account for irregular EHR documentation of housing status and possible imbalance between HEVs retained in HUD-VASH vs. those who exited and became homeless, the model will be weighted using inverse intensity weighting (IIW); IIW reduces bias induced by outcome-dependent assessment times in longitudinal studies [49–51] and has precedent in studies leveraging EHR data to evaluate VA homeless programs. For each HEV, the weighted model will be used to estimate the counterfactual probability of being homeless each day over 1 year follow-up for the REP, REP + CE, and the comparison group of sites not engaged in CARE-VASH [52–54]. The expected number of days homeless for each group will be calculated as the sum of the daily probabilities. The treatment effects for each level of intervention will be estimated as the mean difference in the expected number of days homeless had the HEV enrolled in a site with REP or REP + CE, respectively, compared to the expected number of days homeless had they enrolled in a comparison group site. Non-parametric bootstrapping will be used to calculate simultaneous 95% confidence intervals for the two treatment effects.

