## Methods

### Overview

We will conduct a cluster-randomized trial comparing sites (or clusters) randomized to REP versus REP + CE. Specifically, we will conduct a type 3 hybrid implementation-effectiveness trial [14] using a stepped wedge design with randomization at two levels: implementation start date (3 cohorts) and implementation strategy (REP vs. REP + CE). We will use stratified block randomization to balance site size among sites receiving each strategy across cohorts. We will use mixed methods to assess the impacts of REP vs. REP + CE. We hypothesize that REP + CE will have higher implementation costs than REP, but result in improved and more equitable EBP reach, adoption, sustainment, and housing outcomes, leading to a business case for REP + CE.

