### Participating sites

We identified 12 geographically diverse HUD-VASH implementation sites; each is nested in a division of a VA healthcare system and is comprised of ≥ 1 HUD-VASH team. Collectively, these sites serve ~7908 HEVs/year. Each site will implement MAT and CBT-SUD. Of note, our sample size (12 sites) was pre-determined by our funder.

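### Days homeless: the REP + CE v REP contrast is given no interval, and the two effects that are defined rest on a non-randomised national comparison

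*Protocol article*

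**What the plan says.** The Housing stability section sets the rank of the outcome: "We conceptualize housing stability as our primary effectiveness outcome". It defines the impact on housing for Veterans at REP and REP + CE sites "versus the expected number of days homeless had they enrolled in a comparison group of all sites not engaged in CARE-VASH".

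One weighted logistic model is fitted to daily homelessness status. Its exposure is a three-level site-assignment indicator (comparison group, REP, REP + CE). Besides Veteran characteristics and comorbidities, it adjusts for "temporal trends in the risk of homelessness, and variation across sites". Daily probabilities are predicted for each Veteran under all three assignments and summed over the year. Then: "The treatment effects for each level of intervention will be estimated as the mean difference in the expected number of days homeless", with REP and REP + CE each set against a comparison-group site. On inference: "Non-parametric bootstrapping will be used to calculate simultaneous 95% confidence intervals for the two treatment effects".

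Elsewhere, the Overview hypothesises that REP + CE, relative to REP, will "result in improved and more equitable EBP reach, adoption, sustainment, and housing outcomes". Aim 2, at the end of the Background, is to compare REP with REP + CE and lists Veteran outcomes. The third goal under Evaluation is also a comparison of Veteran outcomes achieved by the strategies. On how the sites came to be included, Participating sites says "We identified 12 geographically diverse HUD-VASH implementation sites" and describes no sampling. Study design gives power as the reason for bringing in all other HUD-VASH sites.

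**The concern.** There are two parts.

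**The strategy contrast.** Strategy is randomised within each stratum-cohort pair of sites, so REP + CE v REP is the comparison that randomisation protects and the one that the hypothesis names. Followed as written, the housing analysis reports two differences from the national sites and no interval for the difference between the arms. That leaves room to judge Consumer Engagement by whether one arm differs clearly from the nation while the other does not, which is not a test of Consumer Engagement.

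**The national comparison.** The 12 sites and the remaining sites were not randomised against each other. A site whose local housing market or team differs from the national picture had that difference before implementation. With a fixed site label as exposure and no named pre-period, the plan as described has nothing that separates a standing difference from an effect of REP or REP + CE.

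**Working it through.** **1. Which contrasts are declared, by outcome**

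| Outcome (section) | REP + CE v REP declared? | Pre-period or differencing named? |
|---|---|---|
| Reach and adoption | Pre-CARE-VASH, REP alone and REP + CE compared; sustainment compared between arms | Yes: pre-period, site and period fixed effects |
| Days homeless (Housing stability) | No: two effects, both against non-CARE-VASH sites | None named |
| Acute care use | Yes, plus CARE-VASH v comparison sites | None named |
| Utilisation costs (Budget impact analysis) | Yes | Yes: difference-in-differences |

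Housing is the row where the comparison between arms is not declared.

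**2. Is the contrast available from the model?** Write D(a) for the mean expected days homeless had all Veterans been at sites of type a. The declared effects are

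- E1 = D(REP) − D(comparison)
- E2 = D(REP + CE) − D(comparison)

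so E2 − E1 = D(REP + CE) − D(REP). The point estimate is a subtraction. Its interval is not: Var(E2 − E1) = Var(E1) + Var(E2) − 2 Cov(E1, E2), and the two effects share a reference group. A reader given only the two intervals cannot recover the third. The same bootstrap replicates would supply it.

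**3. Can adjustment for variation across sites remove standing site differences?** Let A_j be the assignment of site j, constant over all its rows, and write logit P = α_j + βA_j + covariates + time trend.

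- With site fixed effects α_j, each column of A is a sum of site dummies, so β is not identified.
- With random α_j, β is identified only by assuming that α_j is independent of A_j, which is the assumption in doubt for non-randomly selected sites.
- Inverse intensity weighting corrects for when housing status is recorded. It does not address which sites were chosen.

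If pre-implementation rows are included and A_jt switches on at each site's start date, A_jt varies within site and β is identified alongside α_j.

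**4. Size.** The article states no sample size, power or effect size for days homeless, so there is no housing figure to reproduce. For scale, assume a gap g in daily homelessness risk between the 12 sites and the others that remains after covariate adjustment:

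- g = 0.01: 365 × 0.01 = 3.65, about 3.7 days a year
- g = 0.02: 365 × 0.02 = 7.3 days a year
- g = 0.05: 365 × 0.05 = 18.25, about 18.3 days a year

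A gap common to both arms enters E1 and E2 alike and cancels in E2 − E1. Differences specific to single sites do not cancel exactly; they remain as chance imbalance between 6 and 6 sites.

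**5. Precision of each contrast**, as the difference detectable with 80% power at two-sided 0.05, in units of the between-site SD:

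- 6 v 6 sites, 10 df: (2.228 + 0.879) × √(2/6) = 1.79; with 7 df, 1.88
- 6 v 100 sites (number assumed): (1.960 + 0.842) × √(1/6 + 1/100) = 1.18
- 6 v a very large number: 2.802 × √(1/6) = 1.14

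With normal quantiles throughout, 6 v 6 gives 2.802 × √(2/6) = 1.62. Either way the randomised contrast is clearly less precise.

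**The case against.** The strongest reply is that nothing essential is missing. The model has all three levels, Study design announces a three-way comparison, and the opening sentence on housing impact mentions REP vs. REP + CE. This stands in part. A reader might infer that the plan cannot estimate REP + CE v REP or has abandoned it; the documents do not support that. What is missing is its declaration as an effect and its interval, and the sentence on intervals counts two effects.

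Second, the national comparator is a declared choice made for power, with 12 sites fixed by the funder and reach as the trial's primary outcome. This stands as a reason to keep the national comparison, and it tells against making the 6 v 6 contrast the only primary housing effect. It does not justify leaving that contrast undeclared, and adding comparison sites reduces variance, not bias.

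Third, the article lists its covariates only in general terms, so a fuller document may include prior housing or an earlier period. This also stands. A reader might infer that no baseline enters the model at all; the text supports only that none is named.

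Other tempting readings also go too far. The article says that the sites were identified, not how, so it cannot be said that they were picked for favourable outcomes. Strategy is not the only randomised element, since start date is randomised too. No rule in the article judges Consumer Engagement by comparing each arm's significance against the nation; that is a risk left open by the missing interval.

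**Conclusion.** The point holds in two parts of unequal strength.

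The firm part rests on explicit text. For the primary effectiveness outcome, effects and simultaneous intervals are fixed for two comparisons with non-CARE-VASH sites. The randomised strategy contrast in Aim 2 and the hypothesis has neither a declared effect nor an interval.

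The second part is conditional. The two declared effects are observational, and with a fixed site label and no named pre-period they cannot be separated from lasting site differences that Veteran covariates miss. The possible shift of about 3.7 to 18.3 days a year rests wholly on an assumed residual gap of 1 to 5 percentage points. The documents do not show that any such gap exists, or in which direction. REP + CE minus REP is protected from a gap shared by the arms, at the price of a detectable difference of about 1.8 between-site SDs and some chance imbalance.

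**What to change.** 1. Declare REP + CE minus REP in expected days homeless, from the same model, as a pre-specified housing effect and as the basis for any claim about Consumer Engagement. Use a bootstrap that resamples sites, and let the simultaneous 95% intervals cover three contrasts. State that this contrast is imprecise with 6 v 6 sites and that chance imbalance between arms remains.

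2. Keep the comparison with national sites for power, but label it observational. The housing dataset is described as one that "provides longitudinal housing data for all HUD-VASH Veterans available for research studies". Where it holds earlier data, include a pre-implementation period for all sites, with site effects and an indicator that switches on at each site's start date. The estimate is then a difference-in-differences, in line with the reach and cost analyses. State that it assumes parallel trends between CARE-VASH and other sites. If the full protocol already includes such a period, the article needs only to say so.

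**Cost.** No change to design, sites or data collection. The simultaneous intervals widen slightly: as a rough guide, the Bonferroni critical value goes from 2.24 for two contrasts (0.05/4 per tail) to 2.39 for three (0.05/6 per tail), about 7%. The pre-period needs some extra extraction and analysis; the article does not say how far back the dataset goes.

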#### Acute care use

We anticipate that HEVs who receive MAT and/or CBT-SUD will have decreased ED visits and hospitalizations associated with primary SUD diagnoses. We will use the VA Managerial Cost Accounting (MCA) database to compare use of these services among HEVs in HUD-VASH at sites receiving REP vs. REP + CE; and among HEVs at CARE-VASH vs. comparison sites. Differences in acute care use among HEVs at REP, REP + CE and comparison sites will be examined using negative binomial regression models with offsets for the time period each HEV is under observation.

#### Veteran and HUD-VASH staff experiences

We will conduct semi-structured interviews with HEVs with SUDs at implementation sites at baseline and 18 months, characterizing and comparing HEVs’ experiences of and satisfaction with HUD-VASH and SUD services, and factors influencing those experiences, pre- and post-EBP implementation; 18-month interviews will also assess HEVs’ experiences with CE and perceived impacts at sites with the REP + CE strategy. We will use semi-structured interviews with HUD-VASH staff at implementation sites at baseline and 18 months to characterize provider experiences with REP and peers’ experiences with CE. Interviews will also assess experiences of and satisfaction with providing HUD-VASH services to HEVs with SUDs pre- and post- implementation, as well as factors that influence those experiences. We will assess differences in staff experience between sites that received REP vs. REP + CE, stratifying experiences by valence. Interviews will be integrated with periodic reflections to assess contextual and strategy factors associated with HEV and staff experiences.

#### Economic evaluation

We will assess the costs, cost offsets, and non-financial benefits of the EBPs’ sustainment and spread in HUD-VASH; and the budget impact of REP vs. REP + CE.

##### Assessing MAT and CBT-SUD Costs as actually implemented

The predominant cost of delivering MAT and CBT-SUD in HUD-VASH programs is prescriber time and case manager time, respectively. We will use VA administrative data to identify visits in which MAT was prescribed or CBT-SUD was delivered. Interviews with HUD-VASH prescribers will be used to estimate minutes/visit spent on MAT; at implementation sites, we will add a mandated field to templated CBT-SUD notes that indicates time spent outside the encounter. We will multiply employee hourly wages by average time spent on each EBP. Data from 18-month HUD-VASH staff interviews will be used to glean contextual factors that may influence clinical and case manager activities.

##### Costs of implementation strategies

We will use the Implementation Activity Log to draft a list of tasks performed by each CARE-VASH implementation team member. Prior to cohort 3, implementation team members will refine and finalize their task lists; we will input these tasks into software which allows each team member to submit weekly time logs customized to match their task list, recording daily time spent on each task, with the ability to also specify tasks not on the pre-specified list. We will link these data to team members’ hourly costs. To decrease time tracking burden among academic detailers who are engaged in the strategy but external to CARE-VASH, we will use a brief cost capture template at 9 months post-implementation. This template delineates time spent on specific clinical activities and is derived from a practical guide to costing behavioral interventions [55]; the web-based form that captures the template will also query these detailers’ location and hourly salary/fringe. Peers engaged in CE will report time spent/week in a Microsoft Teams poll administered during learning collaboratives.

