**Methods:**

We will use Replicating Effective Programs (REP) to implement MAT and CBT-SUD at 12 sites over 18 months. After 9 months of REP alone, half (n = 6) of these sites will also receive Consumer Engagement (CE) for 9 months, activating HEVs to adopt these practices via peer coaching. We will conduct a type 3 hybrid cluster-randomized trial to compare the impacts of REP versus REP + CE. Randomization will occur at two levels: implementation start date (3 cohorts) and the implementation strategy (REP versus REP + CE). We will use stratified block randomization to balance site size among sites receiving each strategy across cohorts. We will use mixed methods to assess the impacts of REP versus REP + CE on implementation outcomes (reach [primary outcome], adoption, and sustainment); Veteran outcomes (primarily housing); provider and Veteran experiences; and costs and budget impacts. We hypothesize that REP + CE will have higher implementation costs than REP but result in improved MAT and CBT-SUD implementation and Veteran outcomes, leading to a business case for REP + CE.

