#### REP specified for MAT implementation

Since low MAT adoption has been attributed in part to clinicians’ knowledge and training gaps—and AD trains clinicians in the use of novel evidence-based medications—AD will be incorporated into REP for MAT. AD uses 1:1 or small group training, audit-and-feedback tools, and clinician-targeted handouts to influence clinicians to use EBPs. These materials will be available on an online CARE-VASH toolkit once finalized. Current VA dashboards (detailing eligible patients by provider and by division) for MAT [30] will be adapted for HUD-VASH during REP pre-implementation. These dashboards will support educational outreach to prescribers (physicians and physician extenders) who treat HEVs in HUD-VASH with AUD and OUD. Outreach will be delivered by pharmacists trained in AD and with expertise in SUDs. Though the frequency and content of outreach will be determined during pre-implementation, we anticipate individual and small group virtual sessions with prescribers, employing scripts and messaging tailored for CARE-VASH. To enable sustainment, prescribers will be able to receive training from these pharmacists throughout CARE-VASH maintenance. Prescribers will use MAT with HEVs as part of their routine care of HEVs, which encompasses in-person and virtual individual visits, in the clinic or in the field (e.g., home visits). MAT is ideally delivered longitudinally as AUD and OUD are chronic illnesses.

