#### MAT and CBT-SUD reach, adoption, and sustainment

Table 3 lists measures for reach, adoption, and sustainment. Measures of reach for MAT indicate one prescription (30–90 days/duration) and use of MAT for 180 days [40]. For CBT-SUD, reach assesses a single visit and a threshold of 9 visits (which may equate to meaningful impacts in substance use/functioning) [41]. We will use VA administrative data to abstract these measures for HEVs in HUD-VASH at implementation sites. Sustainment will reflect these reach and adoption measures after our intensive implementation supports end (cross-sectionally at 9 months after we end each implementation cohort).

**Table 3 Tab3:** Reach, adoption, and sustainment measures

	**MAT**	**CBT-SUD**
Reach^*^	• % HEVs who used MOUD for OUD, ≥ 1 prescription • % HEVs who used MOUD for OUD for 180 days since initial prescription (without a break ≥ 14 days in supply) • % HEVs who used MAUD for AUD, ≥ 1 prescription • % HEVs who used MAUD for AUD for 180 days since initial prescription (without a break ≥ 14 days in supply)	• % HEVs with SUD with ≥ 1 CBT-SUD visit • % HEVs with SUD with ≥ 9 CBT-SUD visits
Adoption^*^	• % HUD-VASH and mental health prescribers engaged with HEVs^**^ who ordered MOUD/MAUD at least once in the Electronic Health Record	• % HUD-VASH case managers who delivered ≥ 1 CBT-SUD session
Sustainment^¶^	• Reach and adoption measures described above	Reach and adoption measures described above

^*^Reach and adoption measures will be assessed at 18 months post-implementation

^**^Mental health prescribers engaged with HEVs will be defined as prescribers listed on AD dashboards, i.e., most recent mental health prescriber for Veterans who had ≥ 2 billable HUD-VASH encounters in the past year (§B3bi)

^¶^Sustainment will be assessed 9 months after we conclude REP vs. REP + CE for each cohort. HEVs referenced in this table include HEVs enrolled in HUD-VASH at implementation sites

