##### Budget impact analysis

We will also prepare a budget impact analysis (Table 4), characterizing the costs, cost offsets, and non-financial benefits of: MAT and CBT-SUD sustainment and spread in HUD-VASH; and REP vs. REP + CE. We will compare healthcare utilization costs between REP and REP + CE sites using a difference-in-differences research design. This will be performed using both the standard two-way fixed effect approach as well as with the Callaway and Sant’Anna [42] estimator, which takes into account staggered adoption. Our cost analyses will provide data about the magnitude and features of expected EBP costs and benefits. We will assess whether REP + CE yields a sufficient combination of downstream financial cost offsets and non-financial benefits to justify REP + CE vs. REP alone in spreading and sustaining MAT and CBT-SUD. We will also provide information about HUD-VASH site-level contextual factors that may signal an above-average benefit from using REP + CE (vs. REP alone).

**Table 4 Tab4:** Budget impact analysis

Expected resources (costs)		Expected benefits
**Implementation Strategy Costs**	**Care delivery costs**	**Cost offsets and non-financial benefits**
• *Fixed*: Implementation team, HUD-VASH and mental health staff time spent in EBP training • *Variable*: Staff time spent giving/receiving AD and/or CBT-SUD TA, implementation team time spent consulting with HUD-VASH peers, peer time spent delivering CE*	• HUD-VASH and mental health prescriber time spent delivering MAT • HUD-VASH staff time spent delivering CBT-SUD • Downstream healthcare use	• *Cost offset:* decreased use of VA housing services • *Non-financial benefits*: HEVs’ housing stability; improved HEVs’ care experiences; improved HUD-VASH team experiences providing care

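### Academic detailers' time is captured once, at month 9, so no detailer form covers months 10-18, the only period in which REP and REP + CE differ

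*Protocol article*

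**What the plan says.** The abstract's Methods set the timeline. REP is used to "implement MAT and CBT-SUD at 12 sites over 18 months", and "After 9 months of REP alone, half (n = 6) of these sites will also receive Consumer Engagement (CE) for 9 months". Until month 9, all 12 sites are therefore under the same strategy.

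The section on costs of implementation strategies describes three ways of collecting time data:

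- **Academic detailers**, who are external to the project: "we will use a brief cost capture template at 9 months post-implementation". The reason given is to limit their tracking burden. No second administration is mentioned.
- **Implementation team members**: weekly time logs built on task lists drafted from the Implementation Activity Log. On timing, "Prior to cohort 3, implementation team members will refine and finalize their task lists". The software also accepts tasks that are not on the list.
- **Peers delivering CE**: time per week, reported in a poll during the learning collaboratives, which the CE section schedules every two weeks over the nine CE months.

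Two other places bear on the detailer form. The section on REP for MAT says that "prescribers will be able to receive training from these pharmacists throughout CARE-VASH maintenance". Table 4, in the budget impact analysis, lists among the variable implementation costs "Staff time spent giving/receiving AD and/or CBT-SUD TA".

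**The concern.** The plan hypothesises that REP + CE costs more to implement than REP and intends to build a business case on the cost and benefit comparison. Detailing is one of the listed costs. The only stated measurement of detailer time falls at the moment the arms start to diverge, so it describes a period in which both arms receive the same strategy and cannot show a difference that CE produces.

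CE is meant to prompt Veterans to ask their providers for MAT. More prescriber contact with detailers as a result is possible, though the article does not say it will happen. Even if CE leaves detailing unchanged, the amount of detailing in months 10-18 is part of the total strategy cost in both arms. It may not match the first nine months, when prescribers are new to the programme.

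The team time logs raise a lesser concern of the same kind: work done before the task lists are finalised has no task-level record, and the article does not say how it will be costed.

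**Working it through.** The article gives no figure to reproduce here, so the check is one of timing and of counting site-months.

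**Step 1: where month 9 falls.** Table 3's footnotes show how the article counts. One reads "Reach and adoption measures will be assessed at 18 months post-implementation", and 18 months is the full length of the strategy period. Time after the end is worded differently: "Sustainment will be assessed 9 months after we conclude REP vs. REP + CE for each cohort". Nine months post-implementation is therefore nine months from the start, which is the switch to CE.

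**Step 2: site-months.**

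- Whole strategy period: 12 sites × 18 months = 216.
- Months 10-18, both arms: 12 × 9 = 108.
- Under CE: 6 × 9 = 54.

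**Step 3: coverage by the detailer form.** The look-back period is not given. In the most favourable case the form covers all of months 1-9:

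- 12 × 9 = 108 of 216 site-months, or 50%.
- 0 of 54 CE site-months.
- 0 of the 108 site-months in which the arms differ.

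With a second form at month 18, and each form covering its own nine months, these become 216 of 216, 54 of 54 and 108 of 108.

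**Step 4: coverage by the team time logs.** Each cohort has 4 sites (12 sites over 3 cohorts; the periodic reflections section also gives 4 per cohort). Arms are assigned within pairs of sites, so each cohort has 2 REP and 2 REP + CE sites. Assume the logs start when cohort 3 starts.

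- If only cohort 3 work is logged: 4 × 18 = 72 of 216 site-months (33%) and 2 × 9 = 18 of 54 CE site-months (33%).
- If cohorts still running are logged too, the answer depends on the stagger *s* between cohorts. The text does not give it and Fig. 2 is not shown, so it is varied here as an assumption. Cohort *c* is then at month (3 − *c*)*s*, and its logged CE site-months are 2 × max(0, 18 − max(9, (3 − *c*)*s*)).

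| Assumed stagger (months) | CE site-months logged, cohorts 1 + 2 + 3 | Share of 54 |
|---|---|---|
| 3 or 4.5 | 18 + 18 + 18 = 54 | 100% |
| 6 | 12 + 18 + 18 = 48 | 89% |
| 9 | 0 + 18 + 18 = 36 | 67% |
| 12 | 0 + 12 + 18 = 30 | 56% |
| 18 | 0 + 0 + 18 = 18 | 33% |

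**Step 5: what else is recorded.** Peer polls are planned across the CE period at all 6 CE sites. The Implementation Activity Log, described under fidelity, notes when training and TA sessions took place and who attended, with no limit by cohort or month. It is not described as recording preparation or other time outside sessions.

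**The case against.** The strongest reply is that the main cost of adding CE is measured. Peers lead all CE, Table 4 lists their time, and they report it weekly while CE runs. Detailers deliver the REP component that both arms share. Extra Veteran demand would fall first on prescriber time, which the plan treats as a care delivery cost and estimates from administrative visit data and interviews. This stands, and it limits the detailer gap to an indirect arm difference plus the total detailing cost after month 9.

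A second reply is that the single form is a deliberate trade-off to spare external staff, and that Activity Log session records could be combined with month-9 time and wage data. This stands in part: the log is a usable fallback, but the article does not state that step, and session records would miss preparation time. The look-back window and the costing of early team time may also be set out in a fuller document.

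A reader might go further and infer that detailing in the CE phase enters the analysis as zero, that team logs cover only 4 of 12 sites, or that team cost understates early rollout. The documents support none of these. No imputation rule is stated, logs are submitted by team member and are not restricted to cohort 3 work, and no learning effect is shown. Nor does the late log start favour an arm by itself, since each cohort is balanced 2 against 2. The difference-in-differences comparison in the budget impact analysis concerns healthcare utilisation costs and does not use these time data.

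**Conclusion.** The point holds in limited form. As scheduled, the one detailer form sees at most half of the strategy period and none of the 54 CE site-months. Any change in detailing time in months 10-18 goes unmeasured by it in both arms. This rests on reading month 9 as counted from implementation start, which the article's own usage supports, and on a look-back of no more than nine months. The size of the resulting cost error cannot be estimated, because the article gives no detailing hours.

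The team-log point is secondary. Coverage of CE site-months lies between 33% and 100%, depending on a stagger that is not shown and on whether cohorts already running are logged. What is lost is detail on earlier effort; no bias between arms is shown.

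This is a modest weakness in a secondary economic aim. It is worth correcting before launch because time that nobody recorded is hard to recover later.

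**What to change.** Repeat the same detailer form at month 18. State that each form looks back over its own nine months and reports time by site. Report strategy cost by phase (months 1-9 and 10-18) and by arm. The cost is one more short web form per detailer, which largely respects the stated wish to limit their burden.

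For the implementation team, start the weekly logs as soon as a draft task list exists, since unlisted tasks can already be entered. The list is drafted from tasks already performed, so it may not be ready when cohort 1 launches. For any time before the logs begin, state that it will be costed from the Activity Log and name the limitation. This brings forward software already planned and adds a small weekly burden for the team.
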